**Methods/design:**

A 3-arm RCT with waitlist control design will be used in this study. One hundred and fifty three participants will be randomized into (i) Tai-chi, (ii) exercise or (iii) waitlist control groups. Participants in both the Tai-chi and exercise groups will receive 12-weeks of specific intervention, in addition to the standard medication and care received by the waitlist control group. The exercise group will serve as a comparison, to delineate any unique benefits of Tai-chi that are independent of moderate aerobic exercise. All three groups will undergo three assessment phases: (i) at baseline, (ii) at 12 weeks (post-intervention), and (iii) at 24 weeks (maintenance). All participants will be assessed in terms of symptom management, motor coordination, memory, daily living function, and stress levels based on self-perceived responses and a physiological marker.

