## Methods/design

A non-blind, 3-arm randomized controlled trial (RCT) with waitlist control design will be used. Eligible participants will be randomized into (i) Tai-chi, (ii) exercise or (iii) waitlist control groups, on a 1:1:1 basis. The research is conducted in compliance with the Helsinki Declaration, and ethical approval has been obtained from Institutional Review Board of the University of Hong Kong/ Hospital Authority Hong Kong West Cluster (Ref: UW 11–481) before participant recruitment and randomization take place. Human Research Ethics Committee for Non-Clinical Faculties of the University of Hong Kong.

The exercise control will serve as a comparison to delineate the unique benefits of Tai-chi that cannot be accounted for by similar levels of moderate aerobic exercise. This comparison will facilitate a deeper understanding of the positive benefits of Tai-chi, such as attainment of mental tranquility and relaxation, which cannot be explained by physical exercise alone. While exercise is known to confer stress-reducing benefits, there are few studies that compare Tai-chi with alternative exercise interventions [33].

The waitlist control group will continue to receive regular medication and care during the intervention phase. Participants in this group will be offered the Tai-chi or exercise classes on a voluntary basis following completion of the study. Three assessment phases will be carried out for all groups at three time points: (i) baseline, (ii) 12th week (post-intervention time-point), and (iii) 24th week (maintenance time-point).

Figure 1 illustrates the treatment received by the intervention group, the waitlist control condition received by the control group, and the data collection points of the study.

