**Flow diagram of intervention/waitlist control and data collection points.**

### Participant recruitment

Patients diagnosed with chronic schizophrenia, residing in a Hong Kong mental health rehabilitation complex providing both long-term care and halfway house services will be recruited to the study. Patients will be invited to participate by their respective social workers, based on specific inclusion and exclusion criteria.

Inclusion criteria will be as follows: a) fulfillment of DSM-IV TR criteria for schizophrenia, or diagnosis by a psychiatrist, b) age between 18 and 65 years, c) ability to understand and speak Cantonese, and d) no formal training in or regular practice of Tai-chi.

Exclusion criteria will be as follows: a) diagnosis of acute schizophrenia requiring hospitalization, b) presence of unstable or severe schizophrenic symptoms (e.g. persistent withdrawal) that would limit ability to interact or participate in the class, c) history of brain trauma or organic mental disorders (e.g. mental retardation or dementia), d) presence of physical disabilities, e) presence of other severe illnesses which may impair cognitive or visuo-motor function, cause physical pain or limit life expectancy to 10 years or less.

In determining the sample size, we have taken into consideration multiple independent variables, using multiple regression modeling with a medium effect size (f^2^) of 0.15, at 0.8 power and a significance level of 0.05. Experimental, clinical and demographic variables anticipated to affect the intervention outcome were included in the model. An attrition rate of approximately 25% is expected, based on prior community trials of Tai-chi interventions in elderly patients, and exercise programs for patients with severe mental illnesses [33]. Thus, a total of 153 participants will be targeted for the study.

Upon application of inclusion and exclusion criteria, a trained research assistant will obtain informed consent from participants at the rehabilitation complex. Eligible and consenting participants will then be randomized into one of the three treatment conditions, and baseline data collection will be arranged at least one week prior to the commencement of group programs.

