### Instruments

The PANSS is a psychiatric rating system that will be used to assess the positive and negative symptoms of schizophrenia exhibited in the week prior to assessment. It is based on information from the reports of family members or primary care staff, as well as a 40-minute semi-structured psychiatric interview with the patient. The patient will then be rated on a scale of 1 to 7 on 30 different symptoms pertaining to 3 different subscales—positive, negative, and general psychopathology—with internal consistency rats ranging from 0.73 to 0.83.

Assessments will be conducted by trained researchers using the following devices:*Psychiatric Symptoms - The Positive and Negative Syndrome Scale (PANSS 30)* [34]*Motor Coordination and Sequencing – Neurological Evaluation Scale (NES)* [35]2.1Motor Coordination Subscale: motor coordination will be measured using four tasks, including (i) tandem walk, (ii) rapid alternation movements, (iii) finger/thumb opposition, and the finger-to-nose test [36]. The ability of the patient to perform each of the above tasks will be rated on a 3-point scale based on the number of mistakes.2.2Sequencing of Complex Motor Acts Subscale: this will consist of four tasks associated with the sequencing of motor acts, including (i) the fist-ring test (right and left hands), (ii) the fist-edge-palm test (right and left hands), (iii) the Ozeretski test, and (iv) the rhythm tapping test [36]. Performance will be rated on a 3-point scale based on the number of mistakes.

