3.*Digit Span – Wechsler Adult Intelligence Scale, Third Edition – Chinese version (WAIS-III)* [37] *–* The digit span sub-scale is composed of two parts: forward movement of digits, and backward movement of digits. Participants will be invited to repeat movements of 3*–*9 digits forward and 2*–*9 digits backward. Clinically, the sub-scale evaluates participants’ short-term memory, attention, and concentration.4.*Barthel’s Activities of Daily Living (ADL) index – Chinese version (Barthel’s ADL)* [38] Barthel’s ADL index evaluates basic self-care. The index comprises 10 tasks, including feeding, transferring, grooming, toilet use, bathing, walking, climbing stairs, dressing, and bowel and bladder continence. The items are weighted according to a scheme developed by the authors.5.*Lawton’s Instrumental Activities of Daily Living (IADL) scale – Chinese version* [39] – This self-report scale covers 8 domains of complex daily life, such as ability to use the telephone, shopping, food preparation, housekeeping, laundry, traveling on public transport, self-medication, and the ability to handle finances.6.*Stress*6.1Perceived stress scale (PSS) [40] – The PSS measures how often participants experience general stressfulness within a given month on a 10-item, 5-point Likert scale. Higher scores indicate greater stress. The Chinese version of the PSS was translated and utilized by the research team with good internal consistency.6.2Salivary cortisol – Collection will be conducted by participants themselves under the guidance of mental health professionals. Saliva samples will be collected at four prescribed times (upon awakening, 30 minutes post-awakening, at 11:30 am and at 7:30 pm) using the collection device “Salivette” (Starstedt, Ag & Co., Nümbrecht, Germany), which includes a cotton swab to place under the tongue. Smoking, eating and drinking will be prohibited for half hour prior to saliva collection. The samples collected will be stored at −20°C until analysis.6.3Daily condition measures with salivary cortisol – Measures of participants’ health-related behaviors and activities on the day of saliva collection will be collected in conjunction with salivary cortisol. These measures include (i) self-reported sleep quantity that day (hours of sleep at night and nap hours), (ii) subjective sleep quality rated on a scale of 1 to 10, (iii) smoking habit and the number of cigarettes consumed that day, (iv) alcohol/coffee drinking habits and the approximate amount consumed that day, and (v) subjective evaluation of dietary habits and the quality of diet on the day of collection rated on a scale of 1 to 10. All the above measures will affect the diurnal cortisol rhythm and hence must be taken into account during data interpretation.

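### Randomisation is placed before baseline assessment in a non-blind trial, so rated and self-reported baseline scores may be taken with the arm known

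*Protocol article*

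**What the plan says.** The relevant statements are in four parts of the protocol article.

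- **Order of steps (Participant recruitment).** Criteria are applied and consent is obtained. Then: "Eligible and consenting participants will then be randomized into one of the three treatment conditions, and baseline data collection will be arranged". The only timing given for baseline is "at least one week prior to the commencement of group programs". That ties it to the start of classes, not to randomisation.
- **Blinding (Methods/design).** "A non-blind, 3-arm randomized controlled trial (RCT) with waitlist control design will be used". The article states no masking of assessors and no delay in disclosing allocation.
- **How outcomes are obtained (Instruments).** "Assessments will be conducted by trained researchers using the following devices". Of the PANSS it says: "It is based on information from the reports of family members or primary care staff, as well as a 40-minute semi-structured psychiatric interview". Of the NES sequencing tasks: "Performance will be rated on a 3-point scale based on the number of mistakes". Stress is self-reported: "The PSS measures how often participants experience general stressfulness within a given month on a 10-item, 5-point Likert scale". Lawton's IADL is also self-report.
- **Use of baseline (Data analysis).** Effectiveness is explored by repeated measures ANOVA over baseline, week 12 and week 24. Intention-to-treat analysis is invoked against selection bias from discontinuation.

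**The concern.** Baseline taken after randomisation can be acceptable if nobody involved knows the arm. Nothing in the article hides it here. Participants, the care staff who inform the PANSS, and the researchers who rate PANSS and NES could all know the allocation when the baseline score is recorded. All assessments and classes take place in one residential hostel, so word of the arm can travel easily.

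Two things are at stake.

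1. **The reference point for change.** Baseline is one of the time points from which the group-by-time contrast is formed. If disappointment, optimism or rater expectation moves baseline in one arm, and the movement is not equally present later, the difference appears as a difference in change.
2. **Who has a baseline at all.** Someone who learns of an unwelcome allocation may withdraw before the first assessment. That person has been randomised but has no baseline value. Intention-to-treat keeps such a person in the assigned arm but does not supply the missing measurement.

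**Working it through.** **The order as written.** Recruitment lists eligibility, consent, randomisation and then the arranging of baseline. Methods/design declares the trial open. No text shown puts baseline before randomisation or before disclosure. The plain reading is allocation first and baseline second.

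**Which measures are exposed.**

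| Measure | Source | Exposure to knowledge of the arm |
|---|---|---|
| PANSS | interview plus staff or family reports | higher |
| PSS, IADL | self-report | higher |
| NES | researcher rating from counted mistakes | some; the count limits it |
| Digit span | performance test | lower |
| Cortisol | self-collected sample, laboratory assay | lower |
| Socio-demographic and clinical data | records | small |

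**How a shift enters the contrast.** Let b0 be the shift at baseline in one arm relative to another, and b1 the shift at follow-up, both in SD units. With no true effect and equal SDs:

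- change from baseline (group-by-time): bias = b1 − b0
- adjustment for baseline with correlation ρ: bias = b1 − ρ·b0

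If the shift persists fully (b1 = b0), it cancels from the change contrast. If it vanishes by follow-up (b1 = 0), the change contrast carries −b0 and the adjusted contrast −ρ·b0. Only the part that does not persist matters for change.

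**Illustration of the least favourable of these two cases (b1 = 0).** From the documents: 153 participants, 1:1:1 allocation, about 25% attrition, significance level 0.05. Completers are 153 × 0.75 = 114.75, and 114.75 / 3 = 38.25 per arm. Assumed, not in the documents: b0 = 0.1 to 0.3 SD, ρ = 0.5 to 0.9, one pairwise contrast, normal approximation.

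- SE of the change contrast = √(2(1 − ρ) × 2/n)
- SE of the adjusted contrast = √((1 − ρ²) × 2/n)
- error rate = 1 − Φ(1.96 − |bias|/SE) + Φ(−1.96 − |bias|/SE)

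Worked case, b0 = 0.2 and ρ = 0.7:

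- Change: SE = √(0.6 × 2/38.25) = 0.177 and bias/SE = 0.2/0.177 = 1.13, so the error rate is 20.4%.
- Adjusted: SE = √(0.51 × 2/38.25) = 0.163 and bias/SE = 0.14/0.163 = 0.86, so the error rate is 13.8%.

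| b0 (SD) | Change: bias | Change: error rate, ρ = 0.5 to 0.9 | Adjusted: bias | Adjusted: error rate, ρ = 0.5 to 0.9 |
|---|---|---|---|---|
| 0.1 | −0.1 | 7.2% to 16.5% | −0.05 to −0.09 | 5.7% to 14.7% |
| 0.2 | −0.2 | 14.1% to 49.8% | −0.10 to −0.18 | 8.0% to 43.9% |
| 0.3 | −0.3 | 25.9% to 83.5% | −0.15 to −0.27 | 11.8% to 77.3% |

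Adjusting for the affected baseline reduces the bias in this case but does not remove it.

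**Direction.** It is not determined. Higher PSS means more stress. If waitlist participants report more stress at baseline out of disappointment and this fades, their later fall would favour the waitlist arm. Rater expectation could push PANSS either way.

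**Sample size.** The point does not depend on the figure of 153, and the remedy does not change it.

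**The case against.** The case on the other side has several parts.

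- **The order is not airtight.** Randomisation and baseline are joined by a simple conjunction, the moment of disclosure is not given, and the flow diagram (Figure 1) is not available here. A full protocol might specify baseline first. This stands as a limit on certainty about practice. But no text shown supports that order, and the sentence fixes a sequence rather than leaving one out.
- **Baseline is still before treatment.** A reader might infer that it no longer counts as a pre-treatment measurement. The text does not support that. Baseline falls at least a week before classes, so the intervention cannot affect it. Only expectation or selection could.
- **A shift may cancel.** The trial is as open at weeks 12 and 24 as at baseline. A constant shift drops out of the change contrast. This stands, and it is why the illustration is conditional.
- **The bias cannot be stated as a share of the planned effect.** One might divide assumed biases of 0.06 to 0.2 SD by a medium difference of 0.5 SD and report 12% to 40%. The protocol's medium effect is f² = 0.15 for a regression with several predictors, which is not a two-group difference of 0.5 SD. Read as a single two-group contrast it would be 2√0.15 ≈ 0.77 SD, and the share would be about 8% to 26%. Neither range rests on a documented shift.
- **Unequal loss is not shown.** Participants are residents, and the waitlist group is offered classes later. The text supports only that loss before baseline may occur and may differ by arm.

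**Conclusion.** The concern holds as a flaw in the stated sequence. The text puts randomisation before baseline in an open trial, without any stated withholding of the arm, and baseline feeds directly into the planned ANOVA. Exposure is mainly in PANSS, PSS and IADL, with some in NES. It is less for the cortisol assay and small for record-based items, so it would be wrong to treat all baseline data as compromised.

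The size and direction of any bias are unknown. The tabulated error rates show what could follow if a shift of 0.1 to 0.3 SD arose in one arm and disappeared by follow-up. They do not estimate what will happen. Whether raters should be masked at weeks 12 and 24 is a separate question, and this point does not rest on it. The order should be settled before enrolment, because analysis cannot fully repair a baseline recorded with the arm known.

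**What to change.** Reword the last paragraph of the section on participant recruitment along these lines: after consent, all baseline assessments (PANSS interview, NES, questionnaires and saliva collection) are completed; participants are then randomised; allocation is disclosed only after baseline is complete and before the first class. If baseline is already done first in practice, the sentence still needs correcting, because it describes the opposite order.

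The cost is a minor scheduling constraint. Allocation and the forming of class groups must be done between baseline and the start of the programmes, and the existing interval of at least one week leaves room for that. Sample size and analysis are unchanged.

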### Intervention

The Tai-chi intervention is based on the first segment of the Wu-style Cheng-form Tai-chi chuan, comprising 22 simple movements [24]. The basic principal of this form is the emphasis on attention and coordination. Learning the names of each move will promote concentration and focus during practice. Results from the pilot study were used to optimize this program, to maximize learning and memory of the movements while encouraging practice. This will involve the use of flash cards with descriptive diagrams of the movement forms. The intervention will be conducted by mental health professionals with formal training in Tai-chi, who have attended 12 training sessions for instructors at the professional Tsui Woon Kwong Tai-chi Institute.

To design a control exercise regime of comparable intensity, a pilot control study was conducted with four schizophrenic patients (two male and two female) with former Tai-chi experience. The patients’ heart rates were measured by a portable heart rate monitor while they practiced a full set of Tai-chi movements. Based on the data collected, a qualified fitness instructor then devised a moderate aerobic exercise routine designed to achieve 50–60% maximal oxygen consumption (VO_2 max_) for the exercise group. The 1-hour exercise intervention, to be led by mental health professionals, will include a warm up, stretching and joint movements (15 minutes), walking (10 minutes), stepping (10 minutes), mild weight training (10 minutes) and cool down stretching (15 minutes).

For both the Tai-chi and exercise groups, a 1-hour weekly class will be held for 12 consecutive weeks. Sessions will be conducted in groups of 20. Participants will also be invited to a 45-minute, twice-weekly training session under the guidance of mental health professionals in between trainer-led classes. The waitlist group will receive routine care and be offered a similar Tai-chi or exercise class after the 24-week assessment period.

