### Data analysis

#### Effectiveness of the Tai-Chi intervention

Repeated measures analysis of variance using SPSS software will be used to explore the effectiveness of the Tai-chi intervention over the three assessment time points, relative to the exercise and waitlist control groups. Ordinary least squares (OLS) regression will be used to assess the relationship between the dependent variables (outcomes) and independent variables (covariates). A model of the role of Tai-chi with respect to other influencing variables, such as clinical prognosis or frequency of practice, will deepen understanding of the true effects of Tai-chi in this clinical population. All levels of significance will be set at p < 0.05. Intention-to-treat analysis will be used to prevent participant selection bias due to study discontinuation.

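### Two of the three arms are taught in classes, but the named analyses treat participants as independent; if outcomes correlate within class, standard errors will be too small, most of all for Tai-chi versus exercise

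*Protocol article*

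**What the plan says.** All references are to the protocol article.

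- **Unit of randomisation** (Methods/design): "Eligible participants will be randomized into (i) Tai-chi, (ii) exercise or (iii) waitlist control groups, on a 1:1:1 basis". The target in Participant recruitment is 153, so 51 per arm.
- **Delivery** (Intervention): "For both the Tai-chi and exercise groups, a 1-hour weekly class will be held for 12 consecutive weeks", and "Sessions will be conducted in groups of 20". There is also supervised practice between classes: "Participants will also be invited to a 45-minute, twice-weekly training session under the guidance of mental health professionals". The article does not say whether that practice follows class lines.
- **Waitlist arm** (Intervention): "The waitlist group will receive routine care and be offered a similar Tai-chi or exercise class after the 24-week assessment period". This arm therefore has no class during follow-up.
- **Analysis** (Effectiveness of the Tai-Chi intervention): repeated-measures ANOVA over the three assessments for effectiveness, and for covariates "Ordinary least squares (OLS) regression will be used to assess the relationship between the dependent variables". The threshold is p < 0.05. Neither method is given a class or instructor term.
- **Multilevel modelling** appears only in the cortisol section, where the two levels are samples within the day and participants.
- **Sample size** (Participant recruitment): a multiple-regression calculation with f² = 0.15, power 0.8 and alpha 0.05, with an expected attrition of about 25%. No design effect is mentioned.

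**The concern.** People taught together share peers, timing and possibly a teacher, so their outcomes may be more alike than those of people in different classes. Here that can happen in two arms but not in the third, which makes the design partially nested. Repeated-measures ANOVA and OLS handle correlation within a person (ANOVA) or none at all (OLS). Neither handles correlation between people in the same class.

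The contrast most exposed is Tai-chi versus exercise, because both sides are clustered. It is also the contrast the trial needs in order to claim a benefit of Tai-chi beyond moderate exercise. A p-value that overstates the evidence would do most harm there.

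**Working it through.** **Inputs.** From the article: 153 participants, 1:1:1, groups of 20, about 25% attrition, alpha 0.05. Assumed: ICC of 0.01, 0.02, 0.05 or 0.10 (none is given), stable class membership, and equal classes.

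**The plan's own figure.** 153 cannot be reproduced uniquely because the number of predictors is not stated. It can be approached: 9 predictors need 114 completers, and 114/0.75 = 152; 11 predictors need 123, and 123 × 1.25 = 153.75, or 154. Neither route contains a design effect.

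**Classes.** 153/3 = 51 per arm. 51/20 = 2.55, so about 3 classes of 17 in each active arm. After 25% attrition, 51 × 0.75 ≈ 38 per arm, and 38/3 ≈ 12.7 per class.

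**Type I error.** This is a large-sample approximation for a difference of two means, not for the full group-by-time F test.

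- Both arms clustered: DE = 1 + (m − 1) × ICC. True type I error = 2 × [1 − Φ(1.96/√DE)].
- One arm clustered (versus waitlist): the same, with (DE + 1)/2 in place of DE.

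Example at ICC 0.05, m = 12.7: DE = 1 + 11.67 × 0.05 = 1.58; √DE = 1.26; 1.96/1.258 = 1.56; error = 11.9%. Versus waitlist: (1.58 + 1)/2 = 1.29; error = 8.5%.

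| Assumed ICC | DE, m = 12.7 | Tai-chi vs exercise | Tai-chi vs waitlist | DE, m = 17 (all 51) | Tai-chi vs exercise, all 51 |
|---|---|---|---|---|---|
| 0.01 | 1.12 | 6.4% | 5.7% | 1.16 | 6.9% |
| 0.02 | 1.23 | 7.8% | 6.4% | 1.32 | 8.8% |
| 0.05 | 1.58 | 11.9% | 8.5% | 1.80 | 14.4% |
| 0.10 | 2.17 | 18.3% | 11.9% | 2.60 | 22.4% |

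A simulation with classes of 13, 13 and 12 and no true effect (20,000 runs) gave 8.0%, 12.2% and 18.7% for Tai-chi versus exercise at ICC 0.02, 0.05 and 0.10, and 6.4%, 8.4% and 12.5% versus waitlist, in line with the table. At the full stated class size of 20 the Tai-chi versus exercise figures for the four ICCs are 7.2%, 9.5%, 16.0% and 25.0%.

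**Detectable difference, Tai-chi versus exercise, 38 completers per arm, 80% power, two-sided 5%.**

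- Independence, 74 df: (1.993 + 0.847) × √(2/38) = 0.65 SD.
- Design effect only: 0.651 × √DE = 0.72, 0.82 and 0.96 SD at ICC 0.02, 0.05 and 0.10.
- Design effect and between-class df: 6 classes less 2 arm means leaves about 4 df. By the noncentral t, the difference is 0.86 SD even at ICC 0, a factor of 0.863/0.651 = 1.33. Applied to the line above, this gives about 0.96, 1.09 and 1.27 SD.

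**The case against.** **The ICC is not in the article.** This stands. A reader might infer that the standard errors are certainly too small. The article does not support that: at ICC 0 the analysis is correct, and at 0.01 with 12.7 completers per class the error is 6.4%, close to nominal. The finding is conditional.

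**The class structure is partly inferred.** This also stands. The article gives group size only. The number of classes, stable membership over 12 weeks and who teaches which class are not stated. If the same staff teach every class of an arm, the teacher is confounded with the arm, and a class effect does not recover that part.

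**A reader might infer bias.** Random class effects do not shift the expected arm difference. They widen its true sampling variation beyond what the model reports.

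**The detail may lie in a full analysis plan.** This carries some weight, since a short article need not list random effects or df methods. It does not dispose of the point, because the article names its methods, and those methods rest on independence between participants. It also adopts a multilevel model for cortisol on grounds of nesting, and describes no class level there.

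**The remedy is weak with so few classes.** This stands. About 6 classes give a poor ICC estimate and about 4 df, so a mixed model alone cannot settle the matter. That argues for showing results over a range of ICCs. It does not argue for fixing the ICC at zero, which is what the named analysis does.

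**Completers or everyone?** The article states intention-to-treat, so the completer figures are one scenario. Analysing all 51 per arm makes classes larger and the inflation greater.

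**Conclusion.** The point holds in conditional form and should be addressed. Individual randomisation, class teaching in both active arms and none in the waitlist arm are stated, and so are analyses that assume independent participants. If outcomes correlate within class, the reported evidence will be too strong.

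Over an assumed ICC of 0.01 to 0.10, with about 13 completers per class, the true error rate runs from 6.4% to 18% for Tai-chi versus exercise and from about 6% to 12% versus waitlist. For Tai-chi versus exercise it runs from 6.9% to 22.4% if all 51 per arm are analysed. These sizes rest on the assumed ICC, on about three stable classes per active arm, and on a two-mean approximation. The article does not show which ICC applies, and the calculation does not show that 153 is a wrong total.

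**What to change.** 1. Record class and instructor for every participant in the active arms, including any change of class.
2. Analyse effectiveness with a partially nested mixed model: a random class effect in the Tai-chi and exercise arms, none in the waitlist arm, and Kenward-Roger or Satterthwaite degrees of freedom. Keep the within-person correlation over the three assessments.
3. Report the estimated ICC with its uncertainty. Because about 6 classes estimate it poorly, also report the arm contrasts over a prespecified ICC range, for example 0 to 0.10, and word the Tai-chi versus exercise conclusion according to how far it survives that range.
4. State the detectable difference with the design effect and with the between-class df, not only under independence.
5. If one instructor leads all classes of an arm, acknowledge that no model can separate the instructor from the treatment.

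**Cost.** Two identifiers, revised analysis wording and no extra participants or staff. The real price is wider intervals and few degrees of freedom: the Tai-chi versus exercise comparison may be able to show only large differences, and the report should say so.
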